### Interim analyses {21b}

There will be no interim analysis.

### Methods for additional analyses (e.g., subgroup analyses) {20b}

We will perform subgroup analyses in patients with and without ELM for primary and secondary outcomes.

To test the hypothesis that MB-PC-related behavioral and neural changes in social cognition as well as changes in biobehavioral synchrony will mediate the effects of the MB-PC intervention, we will test the indirect effect of MB-PC (proposed predictor) on outcome scores via parental social cognition and via biobehavioral synchrony (proposed mediators), respectively in a multiple mediator analysis using ordinary least squares regressions with bootstrapping.

To test the hypothesis that ELM will moderate the effects of MB-PC on social cognition and biobehavioral synchrony, we will calculate generalized linear (mixed) models with history of ELM (yes/no) and intervention group (MB-PC versus SCC+) as between-subject factors. A positive interaction between the factors intervention and ELM will indicate that MB-PC exerts particularly high effects in parents affected by ELM.

### Methods in analysis to handle protocol non-adherence and any statistical methods to handle missing data {20c}

The primary analysis will be based on the intention-to-treat (ITT) principle, aiming to include all randomized patients in the arm they were originally randomised to and irrespective of the amount of treatment actually received. Sensitivity analyses will be performed to investigate the potential impact of missing data, in particular by using pre-specified conservative multiple imputation strategy and a complete case analysis. A per-protocol (PP) analysis will also be performed as sensitivity analysis. Deviations from the protocol that lead to exclusion from the PP set will be detailed in the statistical analysis plan, which will be written prior to any data analysis.

### Plans to give access to the full protocol, participant-level data, and statistical code {31c}

We will offer access to the full protocol, participant-level dataset, and statistical code on demand.

## Oversight and monitoring

### Composition of the coordinating center and trial steering committee {5d}

The Coordination Center for Clinical Trials (KKS) Heidelberg will monitor the study according to its SOPs and adapted to ICH-GCP guideline E6 (R2) to ensure adherence to ethical aspects, patient’s rights, and quality of data documentation.

### Composition of the data monitoring committee, its role, and reporting structure {21a}

An independent Data Safety and Monitoring Board (DSMB) will monitor and supervise the progress of the trial as well as the adherence to protocol. The board will supervise safety data and will be informed about severe adverse advents. In addition, the Scientific Advisory Board of the consortium will be asked for advice in the case of recruitment fails at any site and they should be prepared to provide the funding agency with information. [name]. [name], Child and Adolescent Psychiatry University of Zuerich; [name]. [name], Institute of Medical Statistics, Computer and Data Sciences, University Hospital Jena; and [name]. [name], University of Applied Sciences, Hamburg, are part of the DSMB.

### Adverse event reporting and harms {22}

Severe adverse events (SAE) comprise child endangerment during the intervention period, suicide or suicide attempt with necessity of treatment at a closed ward or a somatic unit during the intervention period and suicide or suicidality with necessity of treatment at a closed ward after dismissal from hospital care until T2. In case of an SAE, a medical doctor of the participating hospitals will be informed to ensure treatment of acute suicidality. Furthermore, the principal investigator will be informed and will subsequently inform the DSMB.

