#### Criteria for discontinuing or modifying allocated interventions {11b}

Before each individual session, patients will be asked about acute suicidality and significant deterioration of psychopathology attributed to the specific study intervention (see also the “Adverse event reporting and harms {22}” section) in which case a medical doctor of the participating hospitals will be informed to ensure treatment of acute suicidality and it will be decided whether participation in MB-PC will be stopped or the session will be postponed. Acute severe somatic illness that makes transfer to another medical department necessary is a further stopping reason.

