### Outcomes {12}

#### Primary outcome measure

The primary endpoint of the RCT is parenting practices measured with the Alabama Parenting Questionnaire (validated German version) [44] at follow-up 14 weeks after the end of intervention (T2, see Fig. 1 and Table 1). A slightly modified version will be used for parents of children between 1.5 and 6 years in which items suitable only for older children are either rephrased (e.g., instead of “You ask your child about his/her day at school,” the modified item is “You ask your child about his/her day at kindergarten.”) or left out as missing values as they could not be rephrased accordingly (e.g., “Your child stays out in the evening past the time he/she is supposed to be home”). In all, of the total of 42 items, 15 items had to be rephrased and four items were omitted in the modified version. The version used for parents of children between 1.5 and 6 years in this study will be validated. The APQ will be administered at T0 (pre-intervention), T1 (post-intervention), and T2 (14 weeks after end of intervention) and is a reliable and valid 42 item self-report scale which measures parenting practices across five domains: parental involvement, positive parenting, poor monitoring/supervision, inconsistent discipline, and corporal punishment. It, thus, incorporates characteristics of parenting behaviors which are relevant for child development and conduct rather than emotional climate in the home and has been used as outcome measurement in several RCTs on parenting support programs (e.g., [45, 46]).

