## Statistical methods

### Statistical methods for primary and secondary outcomes {20a}

Superiority of the MB-PC intervention regarding APQ scores at T2 compared to SCC+ will be tested at a two-sided significance level of 5%. In the primary analysis, we will use data of both the T1 and T2 assessments (to estimate treatment contrast at T2) in a linear mixed-effects model, with all five APQ subscores as dependent variables in a multivariate model to test for global differences between arms, followed by appropriate post hoc tests for the subscores individually [86]. The analysis will include the covariates used for randomization: center, and treatment setting, and as additional covariates the gender of parent and child, the age of child, the baseline value (T0) of the primary outcome (all 5 APQ subscores), and the primary ICD-11 diagnosis at T0. Analyses of secondary outcomes will be conducted analogously. Safety analyses: Frequencies of AEs and SAEs in all randomized participants will be tabulated, separately for intervention and control group and by presumed relation to intervention and severity.

Statistical analysis will use the software R (http://www.R-project.org). All details will be specified in the statistical analysis plan prior to any data analysis.

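### The SAE list names suicide as the only participant death, so a death from any other or undetermined cause is not an SAE and does not trigger the stated report to the DSMB

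*Protocol article*

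**What the plan says.** The section on adverse event reporting and harms {22} defines the SAE by enumeration. For the intervention period it states: "Severe adverse events (SAE) comprise child endangerment during the intervention period, suicide or suicide attempt with necessity of treatment at a closed ward", and the sentence goes on to accept a somatic unit as well. For the later period it adds "suicide or suicidality with necessity of treatment at a closed ward after dismissal from hospital care until T2". No general seriousness criterion precedes or follows the list, and nothing marks the items as examples.

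The same section attaches the reporting route to the occurrence of an SAE: a hospital doctor is informed, and then "Furthermore, the principal investigator will be informed and will subsequently inform the DSMB".

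Two other sections use the same term. The section on the data monitoring committee {21a} says: "The board will supervise safety data and will be informed about severe adverse advents" (the article's spelling). The statistical methods {20a} say: "Frequencies of AEs and SAEs in all randomized participants will be tabulated", by arm, presumed relation to the intervention and severity. The article does not say what counts as an AE.

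The section on discontinuing or modifying the interventions {11b} says that before each individual session "patients will be asked about acute suicidality and significant deterioration of psychopathology attributed to the specific study intervention", and there refers the reader to section {22}. It also says: "Acute severe somatic illness that makes transfer to another medical department necessary is a further stopping reason".

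**The concern.** In most trials any death is a serious event, whatever its cause, so that nobody has to settle the cause before the event is counted. Here a death qualifies only if it falls under suicide. For a child, a death qualifies only if it arises from endangerment during the intervention period.

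The study population makes this more than a formality. The trial takes acutely ill psychiatric patients across the whole diagnostic spectrum, including addiction and schizophrenia, and the Berlin site describes high rates of addiction disorders in its region. Deaths whose intent is unclear are plausible in such a group.

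Two things are at stake. One is event-level notification of the DSMB. The other is the meaning of the SAE comparison between arms: the trial could correctly report no SAE in an arm in which a participant had died.

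**Working it through.** The point rests on comparing sections; no power, sample size or test result enters it.

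**Step 1: event types against the list in {22}.**

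| Event | Intervention period | After discharge, until T2 |
|---|---|---|
| Suicide | listed | listed |
| Suicide attempt needing a closed ward or somatic unit | listed | not named as such; suicidality needing a closed ward is listed |
| Participant death by accident, somatic disease, or overdose of unclear intent | not listed | not listed |
| Participant death of undetermined cause | not listed | not listed |
| Death of the child | only through child endangerment | not listed |

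**Step 2: what follows for an unlisted death.**

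- Notification ({22}): the chain from principal investigator to DSMB starts only when there is an SAE. An unlisted death does not start it.
- Board remit ({21a}): the board has two functions, supervising safety data and being informed of SAEs. The second does not cover an unlisted death. The first might.
- Table ({20a}): AEs and SAEs are both tabulated. An unlisted death is absent from the SAE rows. It could appear among the AEs, but the article does not define an AE, so this cannot be confirmed.

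**Step 3: the cross-reference from {11b}.** That section sends the reader to {22} for deterioration attributed to the intervention. Section {22} does not mention deterioration, so the reference leads to no rule for that event.

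**Step 4: rough size.** From the documents: 260 randomized patients, 5 weeks of intervention and 14 weeks to T2. Person-time, ignoring dropout:

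260 × (5 + 14) / 52 = 260 × 19 / 52 = 95 person-years.

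The documents give no mortality rate. *Assumption:* 0.5 to 2 deaths from any cause per 100 person-years.

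- 95 × 0.005 = 0.5 deaths (0.475 unrounded)
- 95 × 0.02 = 1.9 deaths

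*Assumption:* 30% to 70% of these are not classified as suicide.

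- 0.475 × 0.3 = 0.14
- 1.9 × 0.7 = 1.33

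So 0.1 to 1.3 unlisted deaths would be expected over both arms. With a Poisson count, the chance of at least one is 1 − exp(−0.1425) = 13% at the low end and 1 − exp(−1.33) = 74% at the high end. The range is wide because both rates are assumed.

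**The case against.** The strongest reply is that a journal article condenses the full protocol. The harms section is short, AEs are tabulated without being defined, and the article says that the full protocol is available on request and that monitoring follows SOPs adapted to ICH-GCP. A wider event catalogue may exist there. This stands as a caution, but it does not remove the point. The article does not leave the definition open: it states a specific list, and that list is too narrow on deaths.

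A reader might infer three stronger claims that the text does not support.

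- *That the DSMB hears only of listed SAEs.* Section {21a} also gives the board supervision of safety data in general, and {20a} tabulates AEs in all randomized participants. An unlisted death could reach the board in aggregate. What is missing is the event-level trigger.
- *That the list wrongly omits the protocol's own grounds for stopping treatment.* Stopping criteria and SAE definitions serve different purposes and need not coincide. Suicidality is partly covered in {22}. Suicidality or deterioration leads under {11b} to a decision, which may be only to postpone a session. Counting stops as SAEs would also distort the comparison: the checks precede individual sessions and concern participation in MB-PC, whereas SCC+ adds one 90-minute workshop. Such events would accrue almost only in the MB-PC arm.
- *That deaths will be sorted by someone who knows the allocation.* The list makes inclusion depend on cause, but the article does not say who classifies a death or whether that person is blinded.

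The objection that the size rests on assumed rates is also fair. The low end of the range is close to no event at all.

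**Conclusion.** The point holds for deaths. Under section {22} as written, a participant's death from a cause other than suicide, or from an undetermined cause, is not an SAE, does not trigger the stated notification of the DSMB, and does not enter the SAE rows by arm. The conclusion assumes that the published list is the operative one. If the full protocol already counts death from any cause, the remaining fault is that the article misstates it.

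The expected number is small, 0.1 to 1.3 over the whole trial on undocumented rates, and the conclusion does not depend on it. The case for changing the list is that deaths are rare, important and easy to count without a judgement on cause. The effectiveness analysis is not affected. The mismatch over deterioration between {11b} and {22} is a secondary matter of reconciliation and does not show that either section is wrong.

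**What to change.** Add one category to the SAE list in section {22}: death of the participant, or of the participating child, from any cause, from randomization to T2, defined identically in both arms. It should be reported to the principal investigator and the DSMB when it becomes known, classified by cause afterwards, and tabulated by arm in its own row. The existing categories stay as they are. The category should also cover participants already randomized, so that early and late clusters are counted alike.

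Do not add intervention stops to the SAE list. Separately, reconcile the cross-reference in {11b} on deterioration attributed to the intervention with {22}, which is silent on it. How that is settled is for the investigators.

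The cost is a short amendment, one check of participants already enrolled, and probably no more than a few extra reports. No visit or assessor is added. The SAE count may look slightly less favourable. If the full protocol already contains the category, only the published wording needs correcting.

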### Frequency and plans for auditing trial conduct {23}

During the course of the study, two monitoring visits per trial site will take place in order to verify patient safety and data integrity employing a risk-based approach. Monitoring will be performed by the Coordination Centre for Clinical Trials (KKS) at Heidelberg University Hospital, the monitor is independent of the investigators. The trial might be audited by the sponsor quality management unit (SpoQS) of the Heidelberg University Hospital; auditors are independent of the investigators.

### Plans for communicating important protocol amendments to relevant parties (e.g., trial participants, ethical committees) {25}

Protocol modifications will be submitted to the Ethics Committee of the Medical Faculty at the University of Heidelberg. The managing site at the Department of General Psychiatry at the University Hospital Heidelberg will then communicate the changes to the German Clinical Trials Register. Each study site is responsible in training their study personnel in protocol modifications.

## Dissemination plans {31a}

Results will be published in research publications and conference contributions. In order to disseminate the results beyond the scientific community, the UBICA-II consortium will not only inform study participants via a newsletter about the findings from the study, but the consortium also cooperates with several self-help groups and initiatives throughout Germany (Wildwasser Esslingen e. V., Shadow and Light – Initiative for Peripartum Mental Disorders, Self-Help group Zwickmuehle, Federal Centre for Early Prevention) who have expressed their support of the study. Close cooperation with a local self-help group (Self-Help group Zwickmuehle) allows to integrate peer support in addition to experts’ support in the MB-PC program. We will inform health care providers about the results of this project via the German Association of Psychiatrists (DGPPN) and the German Society of Child Psychiatry and Psychotherapy (DGKJP) as the scientific societies, and the Bundesdirektorenkonferenz and Bundesarbeitsgemeinschaft leitender Klinikaerzte (BDK, BAG) and the Association of Psychiatrists at General Hospitals (ACKPA) as the legal advocacies of psychiatric and child psychiatric hospitals. Based on the results, we plan to disseminate our preventive approach by offering in-house training for relevant institutions of the German welfare (e.g., Early Prevention System) and health system (hospitals) to convey team-based expertise in addition to expert training.

## Discussion

This is the first study to implement MB-PC as an add-on to routine psychiatric hospital care in Germany. It includes MI parents with a focus on those with a history of ELM and thus reaches families with the highest risk of child neglect and abuse. If evidence of effectiveness is found, MB-PC can be directly implemented into standard hospital treatment. The implementation is favored by low costs and takes into account the typical staffing in German psychiatric hospitals. The individual patient participating in MB-PC is expected to immediately benefit from the trial. Besides establishing and evaluating new interventions, it is important to understand the behavioral and neural mechanisms of change induced by this MB intervention and the effect modification by ELM. The present study therefore not only tests the effectiveness of MB-PC but also investigates possible mediators and moderators in sub-studies. Based on the knowledge on such mechanisms of change it will be possible to further improve the intervention and to tailor it to the needs of the affected parents.

The bicenter study has many advantages (such as recruiting participants with a broad range of mental disorders in different socioeconomic backgrounds in Heidelberg and Berlin) but also comes with special demands regarding standardized recruitment and implementation procedures. For this reason, a reliable and close cooperation between the study centers is highly important. To ensure standardization of procedures, staff from both study sites were instructed in joint trainings prior to the start of recruitment to ensure adherence to the treatment manual and the study protocol. Furthermore, a joint databank and detailed protocols for all study parts shall ensure the standardization of procedures at both study sites.

Despite MB-PC and the workshop in SCC+ concentrating on different aspects of parenting (e.g., SCC+ only focuses on positive interactions while MB-PC also takes into account difficult interactions between parent and child) and using specific outcome measures, we cannot completely rule out a possible dose effect. This is due to the present study being the first study to test effectiveness of MB-PC as an add-on to routine psychiatric hospital care and therefore testing it against SCC+. Future studies should compare MB-PC to other, more extensive parenting programs (if available by that point).

### Future impact

During psychiatric treatment, low-threshold access to treatments strengthening parenting abilities is given for severely ill MI parents. Interventions in this population are urgently needed in order to prevent abuse or neglect in children of parents at high risk of child maltreatment.

If MB-PC is shown to be effective, it can be directly and cost-effectively implemented into standard psychiatric hospital care. The present study therefore has the potential to improve the mental health care system, to prevent child maltreatment and to offer a possibility to break the intergenerational cycle of abuse.

## Trial status

Protocol version number and date: Version 1.6, April 26, 2021.

Start of recruitment: 08/2019; expected end of recruitment: 08/2022.

## Data Availability

All investigators will have access to the final trial dataset.

## Abbreviations

MI: Mental illness
ELM: Early life maltreatment
MB-PC: Mentalization-based parenting-counseling
SCC: Standard clinical care
RCT: Randomized controlled trial
ToM: Theory of mind
CIB: Coding interactional behavior-system
fMRI: Functional magnetic resonance imaging
ANS: Autonomous nervous system
AE: Adverse event
SAE: Severe adverse event
ITT: Intention-to-treat
DSMB: Data safety and monitoring board
